## Abstract

**Introduction:**

Exposure to a high volume of vaccine misinformation on social media can have a negative effect on vaccine confidence and rates. To counteract misinformation, we designed a collage of three short, animated story-based (SAS) videos to convey scientifically informed and accessible information about COVID-19 vaccine applicable to a social media context.

**Methods and analysis:**

We will conduct an online randomized controlled trial primarily to: (1) determine the effectiveness of SAS videos in improving COVID-19 vaccine knowledge; (2) evaluate the effectiveness of SAS videos in increasing behavioral intent for COVID-19 vaccination; and (3) quantify people's interest in watching SAS videos about the COVID-19 vaccine. We also aim to identify barriers and facilitators to COIVD-19 vaccinations that have been shown to minimize vaccine hesitancy between vaccinated and unvaccinated populations. Using a web-based recruitment platform, a total of 10,000 adults from the United States will be recruited and randomly assigned to (1) a SAS video collage arm, (2) an attention placebo control video arm, or (3) no intervention arm (1:1:1). Furthermore, we will measure behavioral intent to obtain information on vaccination regarding COVID-19. At the end of the trial, participants randomized to arm 2 and arm 3 will be given the option of watching one of the intervention videos voluntarily to assess participant engagement with SAS videos. Finally, we will assess individual factors associated with vaccine hesitancy - hope, optimism, COVID-19 perceived risks and benefits, self-efficacy, perceived social norms, and trust - and compare vaccinated and unvaccinated participants across the three arms.

**Discussions:**

Evidence-based information from official channels can be complex and inaccessible to the general public, whereas false information on social media is frequently shared in brief postings, images, or videos that can easily reach the general public, thereby rapidly disseminating (mis-)information. To avoid the spread of misinformation, social media may be used to deliver evidence-based and emotionally compelling information in a readily accessible format in order to pre-empt misinformation. Our findings may help inform future SAS efforts addressing COVID-19 and other important public health challenges.

**Ethics and dissemination:**

The study was approved by the Heidelberg University Hospital's Ethics Committee (S-163/2022). The trial was registered with German Clinical Trials Register (www.drks.de) on 5 January 2022: number DRKS00027938. Findings of the study will be published in peer-reviewed scientific publications and possibly presented at scientific conferences.

## Introduction

Vaccination programs are key components in preventing and decreasing the prevalence of numerous vaccine-preventable diseases, and have historically had a considerable impact on public health (1–3). Yet, the COVID-19 pandemic has seen an upsurge in vaccine hesitancy described as a “delay in acceptance or refusal of vaccination despite availability of vaccination services” (1). For individuals, vaccine hesitancy substantially increases the risk for more severe COVID-19 infections. At the same time, a higher number of severe, clinical COVID-19 cases constitutes a significant challenge for healthcare systems (2). Hesitation and lack of trust in vaccines are longstanding problems that impeded prevention efforts during earlier pandemics, including outbreaks of the Severe Acute Respiratory Syndrome (SARS), Ebola Virus Disease, and Middle East Respiratory Syndrome (MERS) (3). A complex range of social and individual factors have been shown to impact vaccine hesitancy, including public health policies, education and income levels, risk perceptions, trust in authorities, and, importantly, misinformation (4). Since the outbreak of the COVID-19 pandemic, false information and speculative reports about COVID-19 vaccines began circulating on social media platforms, threatening to undermine public trust and confidence in vaccines (5, 6). While vaccination rates have increased globally, anti-vaccination efforts and conspiracy theories continue to spread on social media, eroding public confidence in vaccination. Several studies have shown that vaccine misinformation is associated with lower vaccination rates and higher vaccine resistance (7, 8). By the end of 2021, 10.9% of U.S. adults over 18 years old were still hesitant about getting vaccinated against COVID-19 (9). Recent data also reveals that misinformation and hesitancy is spread even among fully vaccinated individuals. Not all people eligible for a COVID-19 booster dose are willing to get it (10). A fully vaccinated individual may accept or reject a booster dose for a variety of reasons, including vaccination-related adverse effects, perceived effectiveness of the booster dose, susceptibility to the respective infection, and safety concerns. Therefore, measures to increase COVID-19 vaccination and counter disinformation cannot be limited to individuals who have never received a COVID-19 vaccination. Numerous studies have reported that misinformation spreads substantially faster, broader, and wider on social media than factual information (11–13). One reason may be that online information provided by official channels is overly complex and inaccessible in comparison to social media posts, which frequently feature visually appealing images or short videos. As this format is more accessible to the general population, it seems to foster the rapid spread of (mis-)information. Existing literature on health communication indicates that using entertainment-education, particularly animated educational videos, is a successful strategy for developing persuasive, evidence-based health messages and promoting health literacy (14–16). According to research, including relevant narratives into health messages may be more effective than presenting health messages as factual arguments alone (17). Social media platforms have the potential to rapidly disseminate short evidence-based educational content, making reliable information about COVID-19 vaccinations more accessible to the general population. Short, animated story-based (SAS) videos, in particular, may be useful as a novel kind of health message approach since they combine instructional content with an entertainment component to match popular content types on social media platforms (18). Research findings suggest that SAS videos are a preferred format among participants for receiving health messages on a wide range of public health topics (18, 19). Furthermore, SAS videos were shown to have a positive impact on health-related knowledge and behavior (19–21).

As part of this study, we prepared a collage of three SAS videos about the COVID-19 vaccine with no audio (just sound effects and background music) that illustrate the importance of getting vaccinated against COVID-19. The employed SAS videos incorporate a variety of audience engagement methods, including culturally agnostic characters and an emotionally compelling soundtrack, that may encourage more users to share the videos on social media (22). We will evaluate the effectiveness of the SAS videos in increasing knowledge about the COVID-19 vaccination, as well as the impact of the SAS videos in changing attitudes and behavioral intent to get vaccinated and learn more about the COVID-19 vaccine. Additionally, we will examine the degree of participants' voluntary involvement, as defined by their willingness to view the SAS videos and the duration of time spent completing the task in the non-intervention arms. Lastly, we will examine the differences in individual characteristics related with vaccine confidence between the three arms - such as hope, optimism, risk and benefit perception, self-efficacy, perceived social norms, and trust. Our findings will support others in developing simple yet effective health communication strategies to address vaccination hesitancy more effectively.

The primary objectives of this study are as follows:

To evaluate the SAS video's effectiveness in:

improving COVID-19 vaccine knowledge.increasing behavioral intent toward COVID-19 vaccine.quantifying intrinsic interest in watching a SAS video about COVID-19 vaccine.

The secondary objective of this study is to explore the differences in individual factors connected to vaccine hesitancy between the three study arms after the interventions, which are equally distributed across groups by randomization.

## Methods and analysis

### Trial design

We will conduct a randomized controlled trial (RCT) following a multi-site, parallel group design with post-trial access to treatment (see Figure 1). After completing demographic, vaccine, and political beliefs surveys, participants will be randomly assigned to one of three arms: an intervention arm exposing participants to the SAS video collage (arm 1), an attention placebo control (APC) arm showing a video of similar length unrelated to the vaccine (arm 2), or a control arm without any intervention (arm 3). We will randomize the participants in a 1:1:1 ratio to the trial arms. In the intervention arm, participants will watch a collage of three SAS videos underlining the importance of COVID-19 vaccination to provide study participants with access to evidence-based information regarding their risk of contracting and spreading the COVID-19 virus (arm 1: COVID-19 vaccine message) (23). In the APC arm, participants will watch a video that shows how important it is to help children find hope in the future (arm 2: no COVID-19 vaccine message) (24). In the control arm, participants will receive no intervention (arm 3: no video). Participants in arm 1 and arm 2 will not be able to pause or skip the video.

**Figure 1 F1:**
[figure not shown]
Design of randomized controlled trials (second randomization is for a list experiment rather than for the group assignment). The order of the attention, knowledge, hope, and optimism questionnaires is sequential, since study participants complete them in succession. Inclusion criteria: Participants must be over the age of 18 (male, female, or other), have a current address in the United States, and be proficient in English.

After watching the video, participants will be asked to complete one attention question, four true/false knowledge questions about the COVID-19 vaccine, 14 Likert scaled questions about COVID-19 vaccine perceived risks and benefits, attitude, self-efficacy, and perceived norms, and 11 additional Likert scaled items indicating their level of hope and optimism. All questionnaires incorporating Likert scaled items were obtained from our prior research and are cited in the following sections that discuss the questionnaire items.

Furthermore, participants in each arm will be asked to complete five list experiments (25). For each list experiment, we randomized participants 1:1 to a control list or a treatment list. The control list consists of a list of four items about behavioral intent, which are unrelated to the COVID-19 vaccine. The treatment list consists of the same four list items as the control group, as well as a sensitive item assessing behavioral intent to get vaccinated and obtain additional information about COVID-19 vaccinations. The list experiment will be employed to decrease social desirability bias, as participants may already be primed to respond positively to questions about COVID-19 vaccines. Following completion of the list experiment, study participants will respond to seven questions regarding their level of trust in governmental bodies, institutions, and health care providers.

Study participants randomized to the APC group (arm 2) or the control group (arm 3) will be given the option to watch the COVID-19 vaccination intervention video as a post-trial access to treatment at the end of the experiment. The participants will be informed that they will not receive compensation for the time spent watching the SAS videos.

Participants are expected to complete the experiment in 10 min or less. If for whatever reason, participants take longer than 45 min to finish the survey, they will be timed out of the online experiment platform and will not be able to take the survey again. The time-out period is intended to prevent participants from clogging the system with incomplete surveys. We are unable to initiate follow-up within the 45-min time restriction due to the participants' confidentiality.

A pilot phase will evaluate the trial setup as described here within a smaller sample size and shorter study duration, to ensure that the main trial proceeds as seamless as possible.

### Study setting

The proposed RCT will be conducted online. The experiment will be designed and implemented using Gorilla (Cauldron Science Limited) (26), a platform for designing and conducting online behavioral experiments. Participants may participate in the study using a mobile phone, tablet or computer.

### Participants

Participants must be over the age of 18 (male, female, or other), have a current address in the United States, and be proficient in English. Participants who do not meet the inclusion criteria will be excluded from the study. We will recruit study participants stratified by age and gender in order to replicate the age-sex distribution of the adult population in the United States, and vaccination status (no doses, one, two, three or more doses received; or tested COVID-19 positive).

### Recruitment

Participants will be recruited using Prolific (Prolific Academic Ltd) (27), an online, academic research platform for recruiting participants for research studies. Participants must create an account on Prolific and provide their personal information. Each user is assigned a unique, anonymized ID. Every 48 h Prolific sends an email to a random subset of all eligible users registered on the platform. Participants are enrolled on a “first come, first served” basis until the recruiting limit is met. Participants who do not match the eligibility conditions are automatically excluded by Prolific. Participants in the study will be paid £1.70 for completing the survey. Prolific will be handling reimbursement of research participants. Participants are not permitted to take the survey twice with the same ID, per the platform's restrictions. Prolific controls the accounts, hence it is impossible for us to determine if a user has many accounts. We are unaware of the platform's methods for preventing such incidents.

#### Blinding

Due to the fact that recruiting will take place on the Prolific platform, study participants will be unable to be identified or data linked back to them. Participants will respond to the survey questions and submit their responses anonymously through the Gorilla platform. Both, study participants and investigators of this study, will be blinded to the allocation status of the participants.

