We will compare the SAS intervention videos about COVID-19 vaccine with an APC video (arm 2), and no video (arm 3). Developed by our co-author (MA) for Stanford Medicine in collaboration with the IASC, UNICEF, and the WHO, the APC video is similar in style to the SAS intervention videos; it is also animated, with a duration of 4 min, and aims to convey messages of hope, solidarity and empowerment to kids and their caregivers (no health or COVID-19 vaccine-related messages). The APC video will mimic the inactive component of the intervention, i.e., the video format, but not the active component of the intervention, i.e., the message about COVID-19 vaccine. This will allow the content effect of the COVID-19 vaccine intervention videos to be isolated.

Lastly, the comparison between the intervention SAS videos against COVID-19 and the no-video task will allow us to measure the total effect of the intervention.

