## Ethics and dissemination

### Ethics and confidentiality

On 5 January 2022 the trial was registered with German Clinical Trials Register (www.drks.de) with the number DRKS00027938. On 4 May 2022, the Ethic Committee of the Heidelberg University Hospital approved this study (S-163/2022). Any alterations to the protocol will be communicated to the aforementioned Ethics Committee. The same committee is in charge of data monitoring and conducts periodic reviews of the protocol's progress and compliance with the declarations. The Declaration of Helsinki's principles and Good Clinical Practice guidelines will be followed.

Written informed consent will be obtained from all participants in this study. Before participants may begin the survey, they must read the study information and consent form on Prolific. The information and consent form details the study's objectives, as well as potential risks and benefits. Additionally, participants will be provided with a link to Prolific's data privacy policy, which they consented to while joining with Prolific. We will offer participants with the PI's (SB) and the Heidelberg Ethics Committee's contact information. We will inform participants that their names may be revealed to us if they email the PI. The study's scientists will maintain the confidentiality of this information. Consent will be obtained by checking a permission box on the consent form.

Only the study management will have access to the code of the pseudonymization. Data will be pseudonymized as soon as possible, according to § 35 Abs. 2 LDSG BW.

Names and all other personal and medical information are subject to confidentiality and to the regulations of the Federal Data Protection Act (Bundesdatenschutzgesetz – BDSG), the General Data Protection Regulation (Datenschutz-Grundverordnung – DSGVO) and State Data Protection Act (Landesdatenschutzgesetzes - LDSG). We will not collect any personal information (such as the participant's name or address) or medical information. Participants will be completely anonymous to the study investigators.

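### The Blinding section claims participant blinding that the video versus no-video comparison cannot have, which leaves the total effect on the directly asked Likert outcomes open to a demand effect

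*Protocol article*

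**What the plan says.** The Blinding section of the protocol article states without qualification that "Both, study participants and investigators of this study, will be blinded to the allocation status of the participants". The sentences before it are about anonymity: because recruitment runs through Prolific, "study participants will be unable to be identified or data linked back to them", and answers are submitted anonymously through Gorilla.

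Other sections describe what participants see:

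- **Trial design, arm 3:** "In the control arm, participants will receive no intervention (arm 3: no video". No sham is described.
- **Trial design and Intervention, arm 1:** a 4-minute collage of three videos promoting COVID-19 vaccination.
- **Intervention, arm 2:** a 4-minute animated film with no vaccine content. "The APC video will mimic the inactive component of the intervention, i.e., the video format, but not the active component of the intervention".
- **Ethics and confidentiality:** everyone has to go through the consent material ahead of the first survey question. On its content the section says: "The information and consent form details the study's objectives, as well as potential risks and benefits".
- **Introduction:** the primary objectives begin "To evaluate the SAS video's effectiveness in", followed by improving vaccine knowledge, increasing intent and quantifying interest in watching.
- **Trial design, text under Figure 1:** after all questionnaires, arms 2 and 3 "will be given the option to watch the COVID-19 vaccination intervention video as a post-trial access to treatment at the end of the experiment".

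Strengths and limitations defines arm 1 versus arm 3 as the total effect, arm 1 versus arm 2 as the content effect and arm 2 versus arm 3 as the attention effect. It also says that randomization will let the investigators isolate the intervention's true effect.

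**The concern.** Anonymity and blinding are different properties. Anonymity keeps the investigators from knowing who a participant is. Blinding of participants keeps them from knowing which condition they received. The article supports the first and asserts the second.

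The distinction matters because many outcomes are participants' own ratings, collected minutes after exposure. Someone who has read the study's objectives and then watched vaccine videos can see which answers the study hopes for. Someone who has watched nothing has no such cue. If arm 1 shifts its answers for that reason, the shift becomes part of arm 1 minus arm 3 and is reported as an effect of the video. Randomization does not remove it, because it arises after allocation.

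The authors recognise this hazard. Trial design and Strengths and limitations both say that participants may be primed to answer favourably, and the list experiments are adopted for that reason. That protection covers behavioral intent only.

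**Working it through.** The plan gives no figure for blinding or for reporting bias, so there is none to reproduce. The check has three parts.

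**1. Can allocation be inferred?**

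| Arm | What is seen after the objectives are read | Masking device |
|---|---|---|
| 1 | Vaccine videos | None needed to recognise the vaccine message |
| 2 | Animated film of similar style and equal length, no vaccine message | Format matched to arm 1 |
| 3 | Nothing | None |

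The attention questions listed under that heading are also arm-specific: one for arm 1, one for arm 2 and none for arm 3. Format matching helps arm 1 versus arm 2 but cannot help arm 1 versus arm 3.

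**2. Which outcomes are exposed?**

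- *Knowledge (first primary).* True/false items scored against correct answers. A wish to please does not supply the right answer, so exposure is lower.
- *Behavioral intent (second primary).* Measured by list experiments, so partly shielded.
- *Engagement (third primary).* The decision to watch and the time spent watching, in arms 2 and 3 only. The arm 1 versus arm 3 contrast does not arise.
- *Risk perception, response efficacy, attitude, self-efficacy, norms (secondary).* Direct ratings without a shield. The Outcomes and Secondary outcome measures sections expect perceptions and norms to change as a result of the intervention. These items are the most exposed.

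The offer of the intervention video comes after the knowledge, Likert, list-experiment and trust items, so it cannot influence them.

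**3. How large would a demand effect need to be to matter?**

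Inputs: 10,000 participants randomized 1:1:1 (Sample size calculation; Trial design), so 10,000/3 ≈ 3,333 per arm, with no attrition. The difference in demand response between arms 1 and 3, *e*, is not in the document. A range of 0.05 to 0.10 SD is assumed.

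- SE of a standardized mean difference = √(2/3,333) = 0.0245.
- Expected z = *e*/SE: 0.05/0.0245 = 2.04 and 0.10/0.0245 = 4.08.
- Probability of two-sided p<0.05 with no true effect ≈ Φ(z − 1.96): Φ(0.08) ≈ 53% and Φ(2.12) ≈ 98%. The opposite tail is negligible.

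Attrition, which the 10,000 is partly meant to absorb, would raise the SE and lower these percentages.

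**The case against.** The strongest case on the other side is that this is a wording slip with little consequence.

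- **No primary outcome is a direct self-rating.** This stands, and it limits the point mainly to the Likert secondary outcomes.
- **The trial is not open-label.** A reader might infer that it is. The documents do not support that: nowhere are participants said to be told their arm or that other arms exist. The consent form is not shown, so its exact wording is unknown, and an arm 3 participant might take the study for a plain survey. This weakens the certainty that allocation is recognised. It does not support the unqualified blinding claim, because nothing described would mask video from no video.
- **The video offer does not unblind the main outcomes.** A reader might count it as a further cause. It follows them and is itself how engagement is measured, so this part of the objection stands.
- **Blinding is not expressly deduced from anonymity.** This is correct, since no connecting word joins the sentences. But no other basis for participant blinding is given.
- **The three effects are already separated.** This is so, and the remark about the true effect is made while describing randomization. The total effect is still presented without saying that it may include a demand effect.
- **Arm 1 versus arm 2 has the same weakness.** In part: only arm 1 sees a vaccine message. That contrast is better protected because the format is matched, but it is not immune.
- **The size is assumed.** This is correct. At 0.05 SD a significant result is close to a coin toss, not assured.

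**Conclusion.** The statement that participants are blinded cannot be reconciled with a no-video arm, a vaccine-video arm and objectives read beforehand. The supportable wording is that arm 1 versus arm 3 is not effectively participant-blinded. The consequence falls mainly on the directly asked, vaccine-related Likert secondary outcomes.

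The size of the bias is unknown. Under the assumed 0.05 to 0.10 SD, with full numbers, a trial with no true effect would reach p<0.05 on such an outcome in about 53% to 98% of cases, against the nominal 5%. This shows how little bias is needed at this sample size; it is not an estimate of the bias present.

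The randomized design remains usable, and the investigators' half of the blinding statement is not disputed here. The participant-blinding claim, and the unqualified reading of the total effect, should be corrected.

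**What to change.** 1. **Blinding section.** Separate anonymity from blinding. State what is masked and from whom, and do not claim participant blinding for video versus no video.
2. **Strengths and limitations.** Qualify the statement on isolating the true effect: arm 1 versus arm 3 includes any demand or expectation effect.
3. **Vaccine-related Likert outcomes.** Rest the effectiveness claim mainly on arm 1 versus arm 2, described as better protected but not immune. Report arm 1 versus arm 3 beside it as the total effect, with the qualification in item 2. Do not apply this to hope or optimism, because the arm 2 video itself conveys hope and is not a neutral comparator there.

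The cost is wording and a notice to the Ethics Committee, which the protocol already requires for any alteration. No extra participants are needed. The downside is a more modest claim for the total effect.
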